**Secondary objectives**		
To compare the functional outcome between people who receive a group exercise and behaviour-change intervention versus group exercise alone following THR or TKR.	Lower Extremity Functional Scale	Baseline; 6 months; 12 months
To compare the disease-specific pain and function between people who receive a group exercise and behaviour-change intervention versus group exercise alone following THR or TKR.	Oxford Hip Score^36^ or Oxford Knee Score	Baseline; 6 months; 12 months
To compare the perceived level of pain between people who receive a group exercise and behaviour-change intervention versus group exercise alone following THR or TKR.	Numerical Rating Scale for Pain	Baseline; 6 months; 12 months
To compare participant’s self-efficacy between those who receive a group exercise and behaviour-change intervention versus group exercise alone following THR or TKR.	Generalised Self-Efficacy Scale	Baseline; 6 months; 12 months
To compare participant’s fear avoidance to movement between those who receive a group exercise and behaviour-change intervention versus group exercise alone following THR or TKR.	The Tampa Scale for Kinesiophobia	Baseline; 6 months; 12 months
To compare participant’s psychological distress (anxiety and depression) between those who receive a group exercise and behaviour-change intervention versus group exercise alone following THR or TKR.	Hospital Anxiety and Depression Scale	Baseline; 6 months; 12 months
To compare participant’s complications and adverse events between those who receive a group exercise and behaviour-change intervention versus group exercise alone following THR or TKR.	Complications or adverse events recorded in the case report forms	6 months; 12 months
To collect cost-effectiveness data (health resource utilisation; direct and indirect costs) of a group exercise and a behaviour-change intervention versus group exercise alone following THR or TKR.	EQ-5D-5L; Bespoke healthcare resource self-reported questionnaire	6 months; 12 months

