### Assessments

#### Baseline assessment

Baseline data will be collected prior to randomisation during the preoperative assessment appointment, once consent has been obtained. This will include: gender, age, measured height and weight, CCI, self-reported presence and location of multi-site joint pain, comorbidities determined from the medical notes, AMTS, employment status and occupation (when appropriate). Participants will also complete measures on: physical activity (University of California, Los Angeles (UCLA) Activity Scale)^25^; physical function (Lower Extremity Functional Scale (LEFS)^26^; disease-specific function (Oxford Hip Score^27^ or Oxford Knee Score^28^); pain (numerical rating scale for pain); self-efficacy (Generalised Self-Efficacy Scale^29^); fear of movement or kinesiophobia (Tampa Scale for Kinesiophobia^30^); psychological distress (Hospital Anxiety and Depression Scale (HADS)^31^); HRQoL (EQ-5D-5L^32^) and the health utilisation questionnaire.

Follow-up data will be collected 6 and 12 months post-randomisation. Questionnaires will be sent to participants by post from the trial office and returned using a pre-addressed, prepaid envelope. If participants have not responded within 14 days of posting, the trial team will attempt to telephone the participant on up to two occasions to remind them to complete the questionnaires. If required, a second postage of the questionnaires will be provided if requested by the participant during these follow-up telephone calls. If participants wish not to complete the questionnaires, they will be provided with the opportunity to complete the UCLA Activity Scale and EQ-5D-5L questionnaires over the telephone. If these methods fail, the participant would be categorised as a non-responder for that time point only.

In an effort to find evidence-based techniques to improve retention and recruitment to RCTs, a study within a trial (SWAT) will be undertaken. This will examine whether there is a difference in questionnaire response rate by printing the UCLA Activity Scale on pink rather than white coloured paper at the 6 month time point. Results of this SWAT will be reported separately to the ‘host’ trial.

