#### Secondary outcomes

LEFS:^26^ This is a valid and reliable measure of functional impairment in patients with lower extremity musculoskeletal conditions (Mehta *et al*, 2016).^35^
Oxford Hip Score^27^ or Oxford Knee Score:^28^ Both measures have demonstrated good validity and reliability for people undergoing THR or TKR.^36^
Numerical Rating Scale (NRS) for Pain: The NRS has been previously reported as reliable and valid to assess pain.^37^
Generalised Self-Efficacy Scale:^29^ This is a reliable and valid measure of self-efficacy.^38 39^
The Tampa Scale for Kinesiophobia:^30^ This is a valid and reliable measure of kinesiophobia.^40 41^
HADS:^31^ This has been shown as a reliable and valid measure of anxiety and depression.^42^
Complications or adverse events (self-reported) which may include: wound or joint infection, joint dislocation, delayed hospital discharge (measured by length of stay), falls or musculoskeletal injuries and exacerbations of multi-site joint pain. Adverse events and serious adverse events will be reported as per the clinical trial unit’s SOP.Health economic and health resource utilisation: We will collect HRQoL using the EQ-5D-5L.^33^ Primary sources (ie, participant log books) will be used to record the duration of the assessment visits, number and duration of scheduled group sessions, equipment, consumables, educational material, behaviour change intervention training time; number and duration of scheduled telephone calls. Frequency of healthcare resource use will be collected through patient self-reported questionnaires at follow-ups. The categories of NHS resource use that will be collected include treatment costs, outpatient visits, any related-inpatient admissions, rehabilitation visits and any treatment for recurrences and adverse events. Non-medical costs such as care giving and productivity loss for those in employment at each follow-up will be collected.

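### The telephone fallback at 6 and 12 months is stated to collect only the UCLA scale and EQ-5D-5L, so participants who use it have no stated solicited record of complications, a self-reported outcome compared between arms

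*Protocol article*

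**What the plan says.** Table 1 of the protocol article lists, as a secondary objective, a between-arm comparison of complications and adverse events. The measure is given as "Complications or adverse events recorded in the case report forms", at 6 and 12 months. The Secondary outcomes section describes how the events are obtained: "Complications or adverse events (self-reported) which may include: wound or joint infection, joint dislocation", with further items after these. It then adds: "Adverse events and serious adverse events will be reported as per the clinical trial unit’s SOP".

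The follow-up procedure is set out under Baseline assessment: "Questionnaires will be sent to participants by post from the trial office and returned using a pre-addressed, prepaid envelope". The column headings of Table 2 give the same postal mode for months 6 and 12. Participants who do not respond within 14 days get up to two reminder telephone calls, and a second mailing if they ask for one. If they do not wish to complete the forms, "they will be provided with the opportunity to complete the UCLA Activity Scale and EQ-5D-5L questionnaires over the telephone". If that also fails: "If these methods fail, the participant would be categorised as a non-responder for that time point only".

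The Statistical analysis section plans frequencies and percentages of complications by arm, with a chi-squared test or logistic regression. It also plans to report missing numbers by arm, to investigate the missingness mechanism, to impute if appropriate, and to run sensitivity analyses.

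**The concern.** The article states what the call contains, and complications are not in it. A trial team member may thus be on the telephone to a participant, collect the primary outcome, and end the call without a stated question on infection, dislocation, falls or injury. That participant counts as followed up for UCLA but has no stated solicited record for the safety comparison.

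This omission differs from leaving out the longer scales. A fallback call can reasonably skip LEFS, HADS or the Tampa scale to save time. A complications list is short, and it is the safety outcome of a trial that encourages more activity in inactive people with comorbidities after joint replacement. If events go unrecorded, the percentages per arm rest on fewer people than the primary analysis, and they could be off if those people differ in risk.

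**Working it through.** **What the passages fix together.** Table 1 requires a comparison of complications between arms at 6 and 12 months. Secondary outcomes calls them self-reported. Follow-up at those times is postal. The fallback names two instruments, neither of which records complications. No second routine contact at 6 or 12 months is described. Hence a participant with telephone data only has a primary outcome and no stated solicited complications record.

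**Relation to the planned loss.** The sample size allows for 20% loss on the primary outcome: 0.20 × 260 = 52, leaving 208. Telephone responders supply UCLA, so they are inside the 208. For complications they are a further loss on top of the 20%.

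**Illustration of size.** The documents give no complication rate and no expected share of telephone responders, so there is no figure of the plan's to reproduce and every input here is assumed. Let p be the true risk among all responders, s the share answering by telephone only, and k their risk relative to postal responders. Suppose no other route captures their events. Then

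- observed risk = p / [(1 − s) + s·k]
- share of events not collected = s·k / [(1 − s) + s·k]

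With p = 15%:

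| s | k | (1 − s) + s·k | observed risk | events not collected |
|---|---|---|---|---|
| 5% | 1.5 | 1.025 | 14.6% | 7% |
| 10% | 0.5 | 0.95 | 15.8% | 5% |
| 10% | 1 | 1.00 | 15.0% | 10% |
| 10% | 2 | 1.10 | 13.6% | 18% |
| 20% | 3 | 1.40 | 10.7% | 43% |

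The last column must not be read as bias. Participants without data leave the denominator as well as the numerator, so with k = 1 some events are lost but the risk estimate is unbiased. With k below 1 the observed risk is too high.

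**Comparison between arms.** If s and k are the same in both arms, both observed risks are divided by the same factor and the risk ratio is unchanged. Distortion needs a difference by arm. With k = 2 and telephone shares of 5% and 10%, the observed risks are 0.15/1.05 = 14.3% and 0.15/1.10 = 13.6%, a spurious gap of about 0.7 points. For scale, take 208 followed up at 1.5:1, about 125 and 83. The standard error of the risk difference is √[0.15 × 0.85 × (1/125 + 1/83)] ≈ 0.051, or about 5 points. A stacked extreme (5% against 20%, k = 3) gives 0.15/1.10 = 13.6% against 0.15/1.40 = 10.7%, about 3 points.

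**The case against.** The best defence is that the call is not the only route. Adverse events also go through the trials unit's SOP, Table 1 names case report forms as the source, delayed discharge is measured by length of stay, and details of additional treatment are collected under Co-interventions. The DSMC reviews safety. The SOP and the full protocol are not shown, and a journal article condenses both. Keeping a last-resort call to core measures is also a recognised way to protect the primary outcome, and missing numbers by arm are already to be reported.

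Much of this stands, and it rules out three stronger readings:

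- A reader might infer that these participants are never asked about complications. The documents do not show that, because the SOP route may reach some or all of them.
- A reader might infer that the postal responders are a healthier subset, so that rates are understated. Nothing in the article describes the health of people who decline the form. Well people who have lost interest are equally compatible with the text.
- A reader might infer bias between arms because only the intervention arm receives three follow-up calls. Those calls should end by about week 16 (start within 4 weeks, six weekly sessions, last call 6 weeks later), before the 6-month form. No link with declining the form is shown.

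The gap itself remains. Nothing shown says that the SOP route asks every participant in both arms at 6 and 12 months. If it relies on staff contact, opportunities differ in this open-label trial: the intervention arm has up to 6 × 30 + 3 × 20 = 240 extra minutes with physiotherapists. Whether that affects reporting is not known, but a question put equally to both arms guards against it. Imputing an event that may be infrequent is a poorer remedy than asking on a call already being made. The content of that call is stated, so this is not a detail left to a fuller document.

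**Conclusion.** The point holds as a limited, avoidable weakness in a stated procedure. The fallback call, as described, obtains a primary outcome without a solicited complications record, so events may be under-ascertained in participants who use it. The direction and size of any selection are unknown, as is any difference between arms. Under the assumed inputs above, the observed risk moves from 15% to 13.6% in the middle case. It does not move at all if telephone responders have the same risk. A modest difference in telephone use by arm gives a spurious gap that is small beside the sampling error. The primary analysis and the sample size are unaffected. It is a cheap improvement that should be made, not evidence that the safety comparison is biased.

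**What to change.** On the same call, in both arms and at both time points, ask a short yes/no list after UCLA and EQ-5D-5L. It should cover the self-reportable items under Secondary outcomes: wound or joint infection, dislocation, falls or musculoskeletal injuries, and worsening of multi-site joint pain. If the call or the SOP already asks this of everyone, say so in the protocol instead. Report the number with complications data by arm and by mode (postal or telephone), and use it as the denominator for the percentages.

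The cost is roughly two more minutes per call (an estimate), a CRF page and a minor amendment. The downsides are a slightly longer call and mixed collection modes for this outcome. Asking UCLA first protects the primary outcome.

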### Outcome measures

The data collection schedule is presented in table 2.

**Table 2 T2:** Data collection schedule

Data	Time points and mode of data collection			
	Baseline	Intervention period	Month 6 post-randomisation	Month 12 post-randomisation
	Face-to-face	Face-to-face	Postal	Postal
Age (years)				
Gender				
Weight (kg)				
Height (cm)				
Admission date				
Operative procedure (THR or TKR)				
Site of joint replacement				
Duration of hip or knee symptoms				
Presence and location of multi-joint pain				
ASA grade				
AMTS				
List of medical comorbidities				
Physiotherapist exercise class log				
Patient in-session and home exercise diary				
Behaviour change intervention log (group and telephone) (physiotherapist completed)				
Charlson Comorbidity Score				
Employment status and current occupation (when appropriate)				
UCLA Activity Score				
Lower Extremity Functional Scale				
Oxford Hip or Knee Score				
Numerical Rating Scale – Pain				
Generalised Self-Efficacy Scale				
Tampa Scale for Kinesiophobia				
Hospital Anxiety and Depression Scale				
EQ-5D-5L				
Health economic/health utilisation questionnaire				
Complications and adverse events				

Shaded areas represent where these data are being collected.

Assessment intervals following randomisation; each follow-up interval ±1 month.

AMTS, Abbreviated Mental Test Score; ASA, American Society of Anesthesiologists classification; cm, centimetres; kg, kilograms; THR, total hip replacement; TKR, total knee replacement; UCLA, University of California, Los Angeles.

#### Primary outcome

UCLA Activity Scale:^25^ This is a reliable and valid self-reported tool to assess physical activity.^33 34^ It assesses global activity levels with a grading system of 1 out of 10 points where one equates to ‘wholly inactive, dependent on others and cannot leave residence’ and 10 refers to ‘regularly participants in impact sports’.^25^

#### Secondary outcomes

LEFS:^26^ This is a valid and reliable measure of functional impairment in patients with lower extremity musculoskeletal conditions (Mehta *et al*, 2016).^35^
Oxford Hip Score^27^ or Oxford Knee Score:^28^ Both measures have demonstrated good validity and reliability for people undergoing THR or TKR.^36^
Numerical Rating Scale (NRS) for Pain: The NRS has been previously reported as reliable and valid to assess pain.^37^
Generalised Self-Efficacy Scale:^29^ This is a reliable and valid measure of self-efficacy.^38 39^
The Tampa Scale for Kinesiophobia:^30^ This is a valid and reliable measure of kinesiophobia.^40 41^
HADS:^31^ This has been shown as a reliable and valid measure of anxiety and depression.^42^
Complications or adverse events (self-reported) which may include: wound or joint infection, joint dislocation, delayed hospital discharge (measured by length of stay), falls or musculoskeletal injuries and exacerbations of multi-site joint pain. Adverse events and serious adverse events will be reported as per the clinical trial unit’s SOP.Health economic and health resource utilisation: We will collect HRQoL using the EQ-5D-5L.^33^ Primary sources (ie, participant log books) will be used to record the duration of the assessment visits, number and duration of scheduled group sessions, equipment, consumables, educational material, behaviour change intervention training time; number and duration of scheduled telephone calls. Frequency of healthcare resource use will be collected through patient self-reported questionnaires at follow-ups. The categories of NHS resource use that will be collected include treatment costs, outpatient visits, any related-inpatient admissions, rehabilitation visits and any treatment for recurrences and adverse events. Non-medical costs such as care giving and productivity loss for those in employment at each follow-up will be collected.

### Data analysis

#### Sample size

Originally, 250 participants (125 per arm) are required to detect a standardised effect size of 0.4 with 80% power and 5% (two-sided) significance, and allowing for 20% loss to follow-up. These calculations are based on the primary outcome, UCLA Activity Scale, at 12 months, assuming a baseline SD of 2.5 and a between-group difference of 1.^33^ The minimally clinically important difference has been reported as a within person difference of 0.92 points.^33^

The sample size was increased to 260 to account for the amendment in randomisation procedure from 1:1 to 2:1 group allocation, as described earlier.

#### Statistical analysis

A detailed statistical analysis plan (SAP) will be drafted early in the trial and will be finalised prior to any primary outcome analysis. This will be reviewed and will receive input from the Trial Steering Committee (TSC) and the DSMC.

All analyses will be undertaken on the intent-to-treat population, that is, patients will be analysed as they were randomised regardless of the treatment received. Sensitivity analyses will be undertaken on the per-protocol population to assess a range of potential biasses that could have resulted from loss to follow-up, protocol deviations and withdrawal (including mortality). Numerical and graphical summaries of all data will be presented including descriptions of missing data at each level.

Estimates of treatment effects will be reported with 95% CIs. The primary outcome measure, UCLA Activity Scale at 12 months post-randomisation, will be analysed using a mixed effects linear regression model adjusted for baseline activity, 6 month time point and the stratification factors. Centre will be included as a random-effect to take account of their potential heterogeneity and type of operation, comorbidity index and other time points (baseline and 6 months) will be included as fixed-effects. Treatment by 6 month time point interaction will also be included in the model to allow time specific treatment effects to be calculated The adjusted difference in the means with corresponding 95% CI will be reported together with the mean and 95% CIs for each treatment group. If not normally distributed, then transformation to normality will be considered. If this is not possible, non-parametric techniques (for example Mann-Whitney or Kruskal-Wallis test) will be used with no adjustment. Consistency of any observed intervention effect will be explored using forest plots for various subgroups including site, type of operation (TKR and THR) and comorbidity index using interactions. No formal testing of interaction effects will be undertaken as the trial is not powered to detect these and the effect of the intervention is expected to be similar in the THR and TKR subgroups, although their baseline physical activity may be different, which will be taken into account in the analysis.

Similar methods will be used to analyse continuous secondary outcomes. Binary and categorical secondary outcomes, such as complications, will be tabulated to show frequencies and percentages in each arm. χ^2^ tests or logistic regression will be used to assess statistical significance.

Missing data will be minimised by careful data management. Missing data will be described with reasons given where available. The number and percentage of individuals in the missing category will be presented by treatment arm.

The nature and mechanism for missing variables and outcomes will be investigated, and if appropriate, multiple imputation will be used. Sensitivity analyses will be undertaken assessing the underlying missing data assumptions. Any imputation techniques will be fully described in the SAP. Subgroup analyses, complies average causal effect analysis and mediation analyses will be undertaken after being fully specified in the SAP. Compliance with the intervention is defined as attending at least four of six group sessions with a minimum of three participants in the group for these sessions and receiving at least two of the three follow-up phone calls. A priori mediation analysis moderators will include self-efficacy, fear avoidance, psychological distress to compare the mediation pathways presented in the BeST (BackSkills Training) intervention^43^ to the PEP-TALK intervention.

All data collected on data collection forms will be used, since only essential data items will be collected. No data will be considered spurious in the analysis since all data will be checked and cleaned before analysis.

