*Change to the randomisation allocation*: An amendment was made to the randomisation ratio in the minimisation algorithm from 1:1 to 2:1 (Experimental Intervention:Usual Care) after 75 participants had been randomised. The expected allocation ratio at the end of the trial is likely to be approximately 1.5:1. This was done to ensure that a greater number of people are allocated to the experimental intervention, which is a group-based intervention. As the experimental intervention was designed to have three or more people per group, early sites have found it difficult to consistently reach this level of participant numbers with the original 1:1 randomisation allocation. This change was made to reduce the risk of small numbers in the experimental group. The Trial Management Group (TMG) agreed this on 15^th^ August 2019. The sample size was increased to 260 to account for this change. This was approved by the sponsor, Data and Safety Monitoring Committee (DSMC) and research ethics committee.

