## Discussion

This paper presents the research protocol for the PEP-TALK trial. Following a THR and TKR, only 50% of people reach WHO recommended levels of physical activity.^15 47 48^ Those who are least likely to meet these levels are people with a higher body mass index and with comorbidities.^49^ These patients have the most to gain from being more physically active. If this trial’s experimental intervention is shown to be effective, this intervention could have a significant and sustained impact on improving the management of comorbidities such as diabetes, cardiovascular diseases, depression and hypertension for over 103 000 people annually in England and Wales.^1^ It is proposed that, in such an instance, this should be considered for implementation in healthcare services. This could help address the global challenge which multi-morbidities and an ageing population are expected to have on health and social care services.

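### Low-severity free improvement: the primary UCLA model could also adjust for baseline BMI, which the trial already measures and the protocol links to low activity

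*Protocol article*

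**What the plan says.** The Statistical analysis section of the protocol article sets out a linear mixed model for the 12-month UCLA score. It adjusts for baseline activity and the minimisation factors. Centre is a random effect, and "type of operation, comorbidity index and other time points (baseline and 6 months) will be included as fixed-effects". The continuous secondary outcomes are to be handled in a similar way. BMI does not appear, and it is not a minimisation factor either; those are hospital site, joint replaced and Charlson index band.

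Two other places bear on this. The Discussion, writing of recommended activity levels after hip or knee replacement, says: "Those who are least likely to meet these levels are people with a higher body mass index and with comorbidities". The Baseline assessment section lists, among items collected before randomisation, "gender, age, measured height and weight, CCI", so BMI can be computed without further data.

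The same Statistical analysis section says that a detailed SAP will be completed before the primary outcome is analysed. That SAP is not at hand.

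**The concern.** The Discussion names two characteristics side by side. One, comorbidity, is an eligibility criterion, a minimisation factor and a model term. The other, BMI, is none of these, and the article gives no reason for the difference.

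In a linear model, adjusting for a pre-randomisation variable that predicts the outcome generally reduces residual variance and narrows the confidence interval for the treatment effect. If BMI predicts the 12-month UCLA score over and above the terms already present, the planned model leaves that variance in the error term although the data to remove it are in hand. What is at stake is a little precision. The validity of the comparison is not in question.

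**Working it through.** **Inputs from the protocol article**

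- Sample size section: "250 participants (125 per arm) are required to detect a standardised effect size of 0.4 with 80% power and 5% (two-sided) significance"; "assuming a baseline SD of 2.5 and a between-group difference of 1"; "allowing for 20% loss to follow-up". No credit for covariate adjustment is stated.
- Same section: "The sample size was increased to 260 to account for the amendment in randomisation procedure from 1:1 to 2:1 group allocation".
- Randomisation section: "The expected allocation ratio at the end of the trial is likely to be approximately 1.5:1".

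**Assumed, because the article gives no value**

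- p, the share of the variance left by the existing terms that BMI explains: 0.01 to 0.05, with 0.10 as an outer case.
- ρ, the correlation of the 12-month score with the covariates already in the model: 0 (no credit) or 0.5.

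**Step 1. Reproduce the plan's figures.** Per arm at 1:1, n = 2(1.960 + 0.842)² × (2.5/1)² = 98.1, so 99. Then 198/0.8 = 247.5, so 248. The t-test version gives 99.08, so 100 per arm, and 200/0.8 = 250, as stated. At 1.5:1 the same formula gives 82 + 123 = 205, and 205/0.8 = 256.25, so 257, which is consistent with 260.

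**Step 2. Planned precision with no covariate credit.** Evaluable: 260 × 0.8 = 208, split 124.8 and 83.2.

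- SE = 2.5 × √(1/124.8 + 1/83.2) = 0.354.
- 95% CI half-width = 1.96 × 0.3538 = 0.694 UCLA points.
- Power = Φ(1/0.3538 − 1.96) = 80.7%.

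**Step 3. Add BMI.** The residual SD becomes 2.5 × √[(1 − ρ²)(1 − p)]. The SE falls by the fraction 1 − √(1 − p), whatever ρ is. The equivalent number of extra randomised participants is 260/(1 − p) − 260.

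| p (assumed) | SE reduction | CI half-width, ρ = 0 | Power, ρ = 0 | Power, ρ = 0.5 | Equivalent participants |
|---|---|---|---|---|---|
| 0 | – | 0.694 | 80.7% | 90.4% | – |
| 0.01 | 0.5% | 0.690 | 81.1% | 90.7% | 2.6 |
| 0.02 | 1.0% | 0.687 | 81.5% | 90.9% | 5.3 |
| 0.05 | 2.5% | 0.676 | 82.6% | 91.8% | 13.7 |
| 0.10 | 5.1% | 0.658 | 84.6% | 93.1% | 28.9 |

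For p between 0.01 and 0.05, power rises by 0.4 to 2.0 points with no other covariate credit, and by 0.3 to 1.4 points if ρ = 0.5.

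**Step 4. Price of the extra term.** Estimating one more coefficient inflates the variance by roughly 1/208 = 0.5%, or about 0.25% on the SE. The table leaves this out. At p = 0.01 it takes back about half of the gain; at p = 0.05 it hardly matters.

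**The case against.** The strongest reply is that nothing here is wrong. Adjusting for the baseline outcome, the minimisation factors and centre is a coherent choice. The 80% power reproduces without any covariate, so no claim in the article depends on BMI. Other baseline items, such as age, gender, pain or self-efficacy, could be proposed on similar grounds. The SAP is not visible and may already add BMI. All of this stands, and it is why the point is an improvement and not an error. What sets BMI apart from the other candidates is only that the protocol itself names it beside a factor it does adjust for.

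Four stronger readings are tempting, and the article supports none of them.

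- *BMI is an established prognostic factor for 12-month UCLA.* The Discussion sentence is about reaching a WHO activity threshold after joint replacement in general. It says nothing about the UCLA score once baseline UCLA and comorbidity are in the model. Eligibility also restricts the trial to inactive or moderately inactive people with a Charlson index of at least 1, so the remaining contribution of BMI may be small.
- *A known amount of precision is lost.* No BMI–UCLA association is given, and every figure in the table depends on an assumed p.
- *Chance imbalance in BMI could move the effect materially.* A two-standard-error imbalance is 2 × √(1/124.8 + 1/83.2) = 0.28 SD. Multiplying by √0.02 to √0.10 and by the full SD of 2.5 gives about 0.10 to 0.22 points. That takes a roughly one-in-twenty imbalance, applies the full SD although p refers to residual variance, and describes an unadjusted effect that is not the planned estimate. The standard error already reflects chance imbalance, so this would count the same thing twice.
- *Heavier participants return fewer questionnaires.* The article does not say so, and it already commits to examining the missing-data mechanism.

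**Conclusion.** The point holds as a low-severity free improvement. The covariate list in the article omits a variable that the protocol links to low activity after joint replacement and that can be derived from data collected before randomisation. The omission does not bias the randomised comparison, contradicts nothing in the article and leaves the stated power intact.

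The possible gain is a standard error about 0.5% to 2.5% smaller and about 0.4 to 2 points of power, before the small cost of the extra term. This assumes that BMI explains 1% to 5% of the variance left by the existing terms, with 260 randomised, 20% loss and 1.5:1 allocation. If baseline UCLA is strongly prognostic, the power gain is smaller because power is already higher. If BMI adds nothing beyond baseline UCLA and comorbidity, there is no gain.

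**What to change.** In the SAP, pre-specify continuous baseline BMI, computed from the measured height and weight, as one additional fixed effect in the primary UCLA model and in the matching models for continuous secondary outcomes. Replace any missing baseline BMI with the mean over all participants, ignoring arm, so that nobody is dropped from the analysis for want of a covariate. Settle this before outcomes are compared by arm, since adding the term later could look data-driven.

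The cost is one line in the SAP and one degree of freedom with about 208 evaluable participants. It needs no new data and no change to trial procedures or sample size. If the SAP already includes BMI, nothing further is needed.
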